### Study Objectives

The primary objective of this study is to evaluate whether the dosage adjustment of VGCV based on TDM in patients undergoing preemptive therapy for CMV is associated with the completion ratio of treatment without adverse hematological effects. Additionally, this study aims to investigate whether dosage adjustments based on TDM can reduce the time required for CMV pp65 negativity or the incidence rate of adverse effects. Factors related to the pharmacokinetics of GCV and the efficacy and safety of preemptive therapy with VGCV will also be investigated. Further, this study will explore the relationship between GCV plasma concentrations obtained from venous blood and DBS whole blood concentrations at each measurement point and the relationship between *NUDT15* genetic polymorphisms and adverse events. Moreover, an exploratory analysis will be conducted to determine the relationship between CMV antigen quantification using CMV pp65 and CMV viral load measured by quantitative CMV DNA polymerase chain reaction (PCR).

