### Intervention

The study schedule is presented in Table 1. Patients will receive VGCV orally at the dosage specified in the package insert, based on creatinine clearance (Ccr) calculated using the Cockcroft-Gault equation [15]. On day 3 following the initiation of VGCV therapy, venous blood samples will be collected before and 2 hours after the morning dose of VGCV. The plasma concentrations will be measured using liquid chromatography-tandem mass spectrometry [16].

**Table 1 table1:** Summary of the study schedule.

		Hospitalization	Preobservation period	Treatment period									Closeout		Postobservation period
				Week 1					Weeks 2-3						
				Day 1	Day 3	Day 4	Day 5	Day 1		Day 2	Day 3				

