Protocol treatment will continue for at least 2 weeks up to a maximum of 3 weeks from the day of VGCV initiation until CMV pp65 is confirmed to be negative. If CMV pp65 is not confirmed to be negative at 3 weeks after the initiation of VGCV, posttreatment will be performed at the discretion of the physician. Additionally, DBS sampling will be conducted 2 hours after VGCV morning dose and before each meal on day 3 after VGCV initiation to investigate the correlation between DBS-derived whole blood concentrations and plasma concentrations. Finger-prick blood will be collected onto filter papers (Whatman 903 Protein saver card), and blood collection will be conducted to ensure a sampling diameter of at least 6 mm. Genetic polymorphisms of *NUDT15* will also be analyzed using blood samples collected in this study. DNA will be extracted from blood samples, and *NUDT15* polymorphisms in c.415C>T; rs116855232 (p.R139C) and c.416G>A; rs147390019 (p.R139H) will be genotyped using a TaqMan genotyping assay (ID: C_154823200_10 and C_162697298_10). The postobservation period will be 2 weeks after the completion of VGCV administration to assess adverse events and relapse of CMV infection.

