Correlation analysis will be performed between plasma obtained by regular venous blood sampling and whole blood concentrations obtained via DBS. A preliminary analysis will be performed in 20 cases, which is half the sample size. If no clear correlation is determined, blood sampling using the DBS method will be discontinued in subsequent studies. Additionally, a simple regression analysis will be conducted with DBS whole blood concentration as the dependent variable and conventional plasma concentration measurements and clinical information as the independent variables.

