AUC is considered as an indicator of the efficacy and safety of GCV, and many blood collection points are required to accurately determine it, which results in significant burden for the patient. In this study, Bayesian estimation using a population pharmacokinetic model aimed at achieving target AUCs was considered useful for TDM with GCV. Several population pharmacokinetic models of GCV after VGCV administration have been reported [10,17-22], but none have been developed in Japan by using rich sampling data. Therefore, we decided to use a model developed for the Chinese population because of its racial proximity [17]. The selected report showed that the optimal sampling points were two (0 and 2 hours) or three (0, 2, and 4 hours) after VGCV administration [17]. In this study, the sampling points were set at the trough and 2 hours after VGCV administration to reduce patient burden.

To ensure high predictive accuracy for the AUC by Bayesian estimation, we required multiple blood samples. DBS sampling has the advantage that blood samples can be collected in a nonclinical setting such as at home, and only a small amount of blood is required for measurement. As multiple blood samples are required to calculate AUC, replacing venous blood sampling with DBS could reduce the physical burden on patients. However, the correlation between plasma concentrations measured by venous blood sampling and DBS whole blood concentrations remains unclear and investigating this relationship could contribute to less invasive TDM interventions.

Recently, pharmacogenomics, which investigates how genetic polymorphisms of metabolic enzymes or transporters influence the variability in drug responses, has attracted attention as a useful tool in personalized medicine. *NUDT15* polymorphisms are involved in the metabolism of thiopurine drugs. Genetic testing for codon 139 polymorphisms is useful for predicting acute severe adverse events for patients with refractory inflammatory bowel disease, acute lymphoblastic leukemia, or other conditions treated with thiopurine drugs [23]. Although recent reports suggest that *NUDT15* polymorphisms influence not only the antiviral efficacy but also the cytotoxic effects of GCV and acyclovir in vivo [14], no human studies have yet been conducted. The exploratory research in this study could provide useful information on the utility of *NUDT15* genotyping in the treatment of VGCV.

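### Continued use of dried blood spots hangs on an undefined correlation criterion, which does not show whether a spot could stand in for plasma in AUC estimation

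*Protocol article*

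**What the plan says.** The Exploratory Analysis section sets the comparison: "Correlation analysis will be performed between plasma obtained by regular venous blood sampling and whole blood concentrations obtained via DBS". A preliminary look takes place at 20 cases, half the sample size, with this consequence: "If no clear correlation is determined, blood sampling using the DBS method will be discontinued in subsequent studies". The section then adds that "a simple regression analysis will be conducted with DBS whole blood concentration as the dependent variable", with plasma concentrations and clinical information as the independent variables.

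Sampling is described in two places. Under Intervention, for day 3, "venous blood samples will be collected before and 2 hours after the morning dose of VGCV". Under Estimated Apparent Clearance, "DBS sampling will be conducted 2 hours after VGCV morning dose and before each meal on day 3 after VGCV initiation".

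The Study Objectives describe the relationship to be explored as that between venous plasma concentrations and "DBS whole blood concentrations at each measurement point". The Discussion explains why it matters: several samples are needed to estimate AUC, and "replacing venous blood sampling with DBS could reduce the physical burden on patients".

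**The concern.** If a spot is to take the place of a plasma sample, its value must yield nearly the same plasma concentration, and hence nearly the same AUC. Correlation answers a weaker question: whether the two measurements rise and fall together. It is unchanged when every spot reading is multiplied by a constant, and it depends on how widely the concentrations are spread.

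Three features of the plan follow from this choice.

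- The decision at 20 cases rests on correlation alone, and what counts as clear is not defined.
- The analysis text does not say whether trough and 2-hour pairs are kept apart. Concentrations differ several-fold between those times, so combining them creates correlation by itself.
- The regression gives the expected spot value for a known plasma value. Later use would need the reverse.

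At stake is a decision to carry forward, or drop, a sampling method on evidence that does not bear on its intended use.

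**Working it through.** **The plan's own figure.** 40 / 2 = 20 cases, as stated. The DBS comparison has no sample size of its own.

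**Inputs.** From Estimated Apparent Clearance: the population model, its interindividual variabilities (27.2%, 153%, 63.1% and 107%) and the AUC target of 40-60 μg·h/mL. Assumed, because the article gives no figure: Ccr uniform from 30 to 110 mL/min, two illustrative dose levels split at Ccr 60, and lognormal DBS error. Day-3 trough and 2-hour concentrations were simulated for 20 patients, with 3,000 to 4,000 replicates. The pre-breakfast spot is taken to coincide with the pre-dose venous sample.

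**1. Correlation does not see bias.** Let DBS = 0.6 × plasma × error, with error CV 20%.
- Correlation over both time points: r = 0.95. The factor 0.6 has no influence on it.
- By time point, error CVs of 15% and 30% give median r of 0.95 and 0.84 at trough, and 0.93 and 0.79 at 2 hours. A 20% error lies between these, so separating the time points does not remove the problem.
- The log SD is √ln(1 + 0.20²) = 0.198. The 95% limits of the DBS/plasma ratio are 0.6 × exp(±1.96 × 0.198) = 0.41 to 0.88, wholly below 1.
- In proportion, ignoring Bayesian shrinkage, a true AUC of 40 reads 0.6 × 40 = 24 and one of 60 reads 0.6 × 60 = 36. Every patient inside the target would appear to be below it.

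**2. What the missing definition can do.** The critical value at two-sided 5% is |r| = t/√(t² + n − 2), which is 0.44 for 20 pairs and 0.31 for 40. In the simulation the median 2-hour/trough ratio is 4.8 (about 4.7 against 1.0 μg/mL). DBS values were shuffled between patients within each time point, so that they carry no information on the individual.

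| Reading of the rule | Uninformative assay passes |
|---|---|
| By time point, P<0.05 | 4.9% (trough), 5.1% (2 h) |
| Combined, P<0.05 | 99.7% (median r 0.64) |
| Combined, r ≥ 0.5 | 89% |
| Combined, r ≥ 0.7 | 29% |

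A check without the pharmacokinetic model, using independent lognormal values, gives a combined P<0.05 pass rate from 28% (ratio 2, CV 60%) to 100% (ratio 5 to 8, CV 30%). An informative but very noisy assay (error CV 100%) passes at P<0.05 in 50% of trials at trough and 39% at 2 hours, against 98.7% combined.

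**3. Direction of the regression.** In the example of step 1 the slope of DBS on plasma is 0.612, and inverting it gives 1/0.612 = 1.63. The direct slope of plasma on DBS is 1.47. The two differ by the factor 1.47/1.63 = 0.90, which is r² (0.95² = 0.90).

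**4. Pairs.** Venous blood is drawn at two times on day 3. Spots are taken at 2 hours and before each meal, so the spots before later meals have no plasma partner. They cannot enter a paired comparison.

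**The case against.** A reader might infer that the rule cannot fail. That needs two premises the article does not contain: that trough and 2-hour pairs are combined, and that P<0.05 counts as clear. The Study Objectives, by referring to each measurement point, lean towards separate analyses. On that reading an uninformative assay passes only about 5% of the time, and the worry about two dependent points per patient falls away. Even with combined data, a threshold of r ≥ 0.7 would stop most such assays. This objection stands.

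A reader might also infer that the regression runs the wrong way and cannot convert a spot into a plasma value. That is too strong. Regressing a new method on the reference is an ordinary calibration set-up, the line can be inverted, and it does estimate the systematic relation between the two. It is simply not the direct prediction model.

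Finally, a reader might take the plan to promise proof of replacement. It does not: the stated aim is to explore a relationship, replacement is given as motive, and dosing in this trial uses plasma. The 40% bias and 20% error are illustrations, not properties of this assay.

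One part is not answered. The article itself names correlation as the measure and ties a decision to it. Correlation misses systematic bias under either handling of time points. An analysis plan that merely supplied a threshold for r would not cure that.

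**Conclusion.** The point holds in limited form. The 20-case decision rests on an undefined correlation criterion, and the planned analyses do not directly address whether DBS could replace plasma for AUC estimation. A method reading 40% low can reach r of about 0.95 and pass. That conclusion does not depend on combining time points. The move from about 5% to nearly 100% false passes does: it applies only if pairs are combined and P<0.05 is the criterion, and its size depends on the 2-hour/trough ratio and the spread between patients.

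The simulated figures rest on the assumed Ccr range, dose levels and error sizes. The work is exploratory and leaves the primary end point and dosing in this trial untouched, so the weight is modest. With 5 of 40 participants enrolled on June 16, 2025, the 20-case look still lay ahead at that date.

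**What to change.** In the DBS part of Exploratory Analysis:

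- State that only the paired pre-dose and 2-hour samples are used, and that they are analysed separately by time point, in line with the Study Objectives.
- Report the DBS/plasma ratio with 95% limits of agreement at each time point.
- Add a regression with plasma as outcome and DBS plus hematocrit as predictors. Hematocrit is already in the laboratory data of Table 1.
- Compare the AUC from DBS-predicted concentrations with the AUC from measured plasma.
- Base the 20-case decision on an agreement or prediction-error criterion that the sponsor chooses and writes down before the look.
- Say whether the rule applies to the remaining participants or only to later studies, and correct the term simple regression, since more than one independent variable is listed.

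The planned correlation and the regression of DBS on plasma can stay as descriptive results. The cost is a little more analysis and no new samples. The DBS result may look less favourable.

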## Introduction

### Background

Cytomegalovirus (CMV) establishes a latent infection after the resolution of acute infection. Its reactivation can occur in patients undergoing immunosuppressive therapy, leading to organ-specific infections such as febrile illness, pneumonia, and retinitis [1]. For patients at high risk of CMV infection, their viral load is regularly monitored. Preemptive therapy is initiated once the viral load becomes detectable, even in the absence of symptoms. Preemptive therapy is effective in preventing the onset of CMV infection and is recommended for patients undergoing hematopoietic stem cell transplant [2-4].

Valganciclovir (VGCV) is the first-line treatment not only for the prevention and treatment of CMV infections but also for preemptive therapy. It is rapidly metabolized to its active metabolite ganciclovir (GCV). Because GCV is primarily excreted by the kidneys, the dose of VGCV is adjusted based on renal function [5]. In patients who have undergone solid organ transplant, a correlation has been reported between the therapeutic effect of GCV on CMV viremia and the area under the concentration–time curve (AUC) [6]. Therefore, sufficient AUC exposure is necessary for adequate treatment. Additionally, the relationship between AUC and adverse effects has been reported [6-9]. These reports suggest that the effective range of GCV is between 40 and 60 μg·h/mL of AUC. However, a significant interindividual variability has been observed in the plasma concentrations of GCV, even when administering the dose specified in the package insert [6,10]. To this end, dosage adjustments based solely on the package insert are insufficient, and the usefulness of therapeutic drug monitoring (TDM) for GCV has been reported [7]. However, the utility of routine GCV concentration measurements and TDM remains controversial and is not currently being conducted [11].

Recently, dried blood spot (DBS) sampling, which involves collecting a small amount of blood from the fingertip onto a filter paper, has been increasingly performed in clinical practice as a less invasive method to facilitate TDM [12,13]. In addition, nudix hydrolase 15 *(NUDT15*) polymorphisms were reported to influence the antiviral efficacy and cytotoxicity of GCV [14]. However, the clinical utility of DBS and measuring *NUDT15* polymorphisms for VGCV treatment has not yet been established.

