**Assessments**															
	Patient’s background^c^		✓												
	CMV^d^ pp65/CMV-PCR^e^		✓					✓				✓		✓	
	Laboratory data^f^		✓	✓	✓	✓		✓				✓		✓	
	Adverse events			✓	✓	✓	✓	✓		✓	✓	✓		✓	
	Concomitant medication		✓	✓	✓	✓	✓	✓		✓	✓	✓		✓	

^a^TDM: therapeutic drug monitoring.

^b^*NUDT15*: nudix hydrolase 15.

^c^Including sex, age, height, weight, medical history, complications, and concomitant medications.

^d^CMV: cytomegalovirus.

^e^PCR: polymerase chain reaction.

^f^Including levels of white blood cell, neutrophil, hemoglobin, platelet, hematocrit, aspartate aminotransferase, alanine aminotransferase, albumin, blood urea nitrogen, serum creatinine, estimated glomerular filtration rate, sodium, potassium, and chloride.

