#### Exploratory Analysis

The median (or mean) of the estimated AUC and dose-adjusted estimated AUC will be calculated for each renal function at the start of treatment (Ccr≤30, 30<Ccr≤60, 60<Ccr≤80, Ccr>80 mL/min). Kruskal-Wallis and Dunn multiple comparisons tests will be performed for each group. A correlation analysis will be conducted between Ccr and the recommended probable dose by using Bayesian estimation. Single and multiple regression analyses with the dose-adjusted estimated AUC as the objective variable and clinical information as the explanatory variables will be performed to explore the factors affecting the dose-adjusted estimated AUC. The proportion of CMV antigen-positive cells that disappear in less than 3 weeks of treatment will be calculated, and a binomial test will be performed against the proportions in the preliminary study. The patients will be grouped according to the presence or absence of disease or CMV infection recurrence, and the median (or mean) of the estimated trough blood concentration, estimated AUC, and total exposure will be calculated in each group. If necessary, the Mann-Whitney *U* test will be performed. The actual total dose of VGCV during the preemptive therapy and the total dose assuming that VGCV is administered at the dose stated in the package insert will be calculated, and a Wilcoxon signed-rank test will be performed. Patients will be grouped according to *NUDT15* genotype (wild-type, homozygous variant or heterozygous variant), and the number and proportion of adverse events in each group will be calculated. Fisher exact test will be performed. Additionally, the median (or mean) estimated trough plasma concentration, estimated AUC, and total exposure will be calculated for each group, and a Mann-Whitney *U* test will be conducted. If both CMV pp65 antigen and CMV-PCR are positive, the correlation will be analyzed using the Spearman rank correlation coefficient. *P* values calculated from the above analyses will be used as references.

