## Discussion

To the best of our knowledge, this is the first study that will investigate the impact of TDM intervention on improving the completion rate of preemptive therapy in patients receiving VGCV. In this study, both patients and investigators are aware of dose adjustments. However, the efficacy and safety of the VGCV therapy will be evaluated objectively by clinical laboratory values and CTCAE version 5.0. Therefore, observer and confirmation bias will not occur.

The use of VGCV as preemptive therapy is not specified in its package insert. Still, it is common based on previous reports in patients who undergo hematopoietic stem cell transplant [2-4], suggesting its effectiveness in clinical practice in Japan. GCV is known to have large interindividual variability in plasma concentrations after oral administration of VGCV. A previous report indicated that patients with impaired renal function experience higher exposure to GCV, whereas those with better renal function experience lower exposure [7]. High plasma concentrations of GCV are associated with an increased frequency of adverse events, whereas low concentrations would lead to insufficient therapeutic efficacy. Therefore, achieving the target AUC through TDM would increase both safety and efficacy.

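### The DBS regression is named as simple (one-predictor), so it cannot show which clinical variables change the DBS–plasma relation; plasma concentration should be in the same model

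*Protocol article*

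**What the plan says.** Under Statistical Analysis, Exploratory Analysis, the article plans a correlation analysis of plasma against DBS concentrations, with a preliminary look at 20 cases that decides whether DBS sampling goes on. It then adds that "a simple regression analysis will be conducted with DBS whole blood concentration as the dependent variable and conventional plasma concentration measurements and clinical information", the last two being the predictors. No multiple regression is named for DBS.

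Earlier in the same section, the regression for exposure is described differently: "Single and multiple regression analyses with the dose-adjusted estimated AUC as the objective variable and clinical information as the explanatory variables". There both forms are named.

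DBS samples are taken on day 3 "to investigate the correlation between DBS-derived whole blood concentrations and plasma concentrations" (end of the section Estimated Apparent Clearance). The Discussion gives the reason: DBS might replace venous sampling and spare the patient. Hematocrit is among the laboratory data (Table 1, footnote f: "Including levels of white blood cell, neutrophil, hemoglobin, platelet, hematocrit").

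On renal function, the Background says "Because GCV is primarily excreted by the kidneys, the dose of VGCV is adjusted based on renal function", and the Discussion cites a report that "patients with impaired renal function experience higher exposure to GCV, whereas those with better renal function experience lower exposure".

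**The concern.** A simple regression has one predictor. Because the article names both forms for exposure and only the simple one for DBS, the natural reading is that plasma and each clinical variable enter separately.

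If DBS is to stand in for plasma, a clinical variable matters when it shifts the DBS value at a given plasma concentration. A regression of DBS on that variable alone answers another question: does the variable go with a high or low ganciclovir concentration? Two things follow.

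- **A real effect can be hidden.** Between-patient variation in ganciclovir concentration stays in the error term and swamps a modest hematocrit effect. This needs no confounding.
- **A spurious factor can appear.** A variable associated with exposure picks up that association even if it has no bearing on the DBS–plasma relation.

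At stake is what the substudy reports about corrections needed before DBS could be used for monitoring.

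**Working it through.** The article gives no power, alpha or sample size for this regression, so there is no figure to reproduce. What follows is an illustration at n = 40 (the planned sample size), two-sided 0.05, one plasma–DBS pair per patient, plasma taken as measured without error.

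**Step 1. What the simple slope estimates.** Let log DBS = log plasma + β·H + e, where H is a clinical variable in SD units. With plasma in the model, the slope for H is β. Without it, the slope is β + δ, where δ is the slope of log plasma on H. The simple slope therefore mixes the effect of interest with exposure. Even when δ = 0, the residual variance rises from σe² to σp² + σe², where σp is the SD of log plasma and σe that of the DBS error.

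**Step 2. A real hematocrit effect, no confounding (δ = 0).** Assumed, not in the article: σp 0.4 to 0.6, σe 0.12 to 0.15, β 0.05 to 0.08 (5 to 8% per SD of hematocrit).

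- Simple: r = β/√(β² + σp² + σe²)
- Joint: partial r = β/√(β² + σe²)
- Power ≈ Φ(atanh(r)·√(n − 3 − k) − 1.96), with k = 0 for simple and k = 1 for joint; the other tail is negligible here except at the smallest r.

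Worked case, β = 0.08, σp = 0.4, σe = 0.12:

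- Simple: r = 0.08/√(0.0064 + 0.16 + 0.0144) = 0.08/0.425 = 0.188; atanh 0.190 × √37 = 1.16; power Φ(−0.80) ≈ 21%.
- Joint: r = 0.08/√(0.0064 + 0.0144) = 0.08/0.144 = 0.555; atanh 0.625 × √36 = 3.75; power Φ(1.79) ≈ 96%.

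Simulation of all corners (8,000 trials each) agrees with the formula to within about 2 percentage points:

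| β | σp | σe | Simple | Plasma in model |
|---|---|---|---|---|
| 0.08 | 0.4 | 0.12 | 22% | 97% |
| 0.08 | 0.4 | 0.15 | 21% | 87% |
| 0.08 | 0.6 | 0.12 | 12% | 97% |
| 0.08 | 0.6 | 0.15 | 12% | 87% |
| 0.05 | 0.4 | 0.12 | 11% | 69% |
| 0.05 | 0.4 | 0.15 | 11% | 51% |
| 0.05 | 0.6 | 0.12 | 8% | 70% |
| 0.05 | 0.6 | 0.15 | 8% | 50% |

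A separate set of assumptions (plasma CV 30 to 50%, DBS error CV 15%, hematocrit SD 5 points, effect 1 to 1.5% per point) gives 8 to 29% for simple regression and 49 to 83% with plasma included.

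**Step 3. A renal variable with no direct effect on DBS.** Inputs from Estimated Apparent Clearance: CL/F = 7.09 × (1 + Ccr/68.3) and interindividual variability of 27.2% (CL/F), 153% (Vc/F), 63.1% (Q/F) and 107% (Vp/F). Assumed: one dose level every 12 hours, and Ccr uniform over 30–60, 60–120 or 40–120 mL/min.

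- The correlation of the log concentration before and 2 hours after the day 3 morning dose with Ccr runs from about −0.14 (2 hours, narrowest range) to −0.41 (pre-dose, widest range).
- Power at r = 0.14: atanh 0.141 × √37 = 0.86, about 14%. At r = 0.41: atanh 0.436 × √37 = 2.65, about 75%.
- The upper end depends on how the variability percentages are coded: taken directly as log-scale SDs they give −0.38, or about 68%.
- With plasma in the model, a renal variable without a direct effect is flagged in about 4 to 6% of trials.

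**Step 4. Effect of dosing by Ccr.** The Intervention section sets the starting dose from Ccr. On the AUC scale, a dose exactly proportional to typical CL/F brings the correlation with Ccr to 0. An assumed halving of the dose below Ccr 60, over the range 40–120, turns it to about +0.2. The sign and size of the spurious association thus depend on the starting-dose rule and the patient mix.

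**The case against.** **The wording may be loose.** The sentence speaks of one analysis with several independent variables, which could mean a joint model, and the article's regression terms vary (*single* in one place, *simple* in another). This stands as a doubt about intent. It does not rescue the text: if a joint model is meant, *simple* is the wrong word and the same sentence needs correcting.

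**A stronger reading is tempting.** A reader might infer that Ccr and other renal markers are bound to appear as DBS factors, in 40 to 92% of trials. The documents do not support that. The range comes from correlating Ccr with AUC (−0.27 to −0.50) at one dose level. The outcome here is a concentration at a fixed time, which also varies through Vc/F, Q/F and Vp/F, so the correlation is weaker. A single dose across the Ccr range also conflicts with the Ccr-based starting dose. The Discussion supports some remaining association, but only in words.

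**Hematocrit is not named in this regression, and its effect size is assumed.** Both are true. It stands as an example of a collected clinical variable. The size of the gain from adjustment moves with the inputs; in every setting tried, the joint model did better.

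**The analysis is exploratory, and an analysis plan not shown may give the covariates.** P values in the exploratory analyses are for reference only, and the paired data would allow a joint model later. That limits the weight of the point. But the issue is not a missing covariate list: the article names a method, and its estimate targets the wrong quantity even when read descriptively.

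**Conclusion.** The point holds in a limited form. As named, the DBS regression cannot tell which clinical variables change the DBS–plasma relation. The firmest part needs no confounding: under the assumptions of step 2, a real hematocrit effect is found in about 8 to 22% of trials by simple regression and about 50 to 97% with plasma in the model. A spurious renal association is possible but neither assured nor fixed in direction. At one dose level it would be flagged in roughly 14 to 75% of trials, and Ccr-based dosing can shrink or reverse it.

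All these sizes rest on inputs outside the article, apart from the pharmacokinetic model and the sample size. The effect is confined to an exploratory result. A reader might infer that it touches the decision to discontinue DBS sampling, but that rule rests on the correlation analysis. The primary end point is also unaffected.

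**What to change.** Replace the simple regression by one multiple regression of log DBS concentration on log plasma concentration, hematocrit and a few clinical variables named in advance. Alternatively, regress the log DBS-to-plasma ratio on hematocrit and those variables. If more than one pair per patient is used, allow for the repeated pairs. If a joint model was already intended, correct the word *simple*.

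The cost is one sentence. Plasma, DBS and hematocrit are already collected, so no extra sampling is needed, and only 5 of 40 patients were enrolled at the last count in the article (June 16, 2025).
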